### Who will take informed consent? {26a}

Consent from potential trial participants will be sought by a member of the local trial team trained in Good Clinical Practice (GCP). This will usually be in a face-to-face setting, during an out-patient appointment, pre-operative assessment or when the participant is admitted to hospital for their surgery. As part of the COVID-19 contingencies, if face-to-face consent is not possible, participants can complete the consent form at home and either post it back to the research team or bring it into hospital with them when they are admitted for surgery.

### Additional consent provisions for collection and use of participant data and biological specimens {26b}

As the most common indication for colectomy will be colorectal cancer, consent includes permission for storage of data to permit subsequent record linkage to analyse cancer-specific outcomes. Consent for this is sought at the time of consent to the main study and is optional.

### Interventions

#### Explanation for the choice of comparators {6b}

Intravenous lidocaine used in this setting is an adjunct to usual anaesthetic and perioperative analgesic practice. There is no alternative medication against which to test the intervention; hence, the comparator is a placebo of physiological (isotonic) 0.9% sodium chloride (NaCl) which looks identical to lidocaine.

#### Intervention description {11a}

In the intervention arm, an intravenous bolus of 2% lidocaine at induction of anaesthesia (1.5 mg/kg ideal body weight) infused over 20 min is followed by intravenous infusion of 1.5 mg/kg/h ideal body weight with a maximum rate of 120 mg/h for a minimum of 6 h up to a maximum of 12 h. Ideal body weight rather than actual body weight is used to prevent the possibility of toxicity by exceeding the upper therapeutic threshold of lidocaine in very overweight patients.

The bolus and intravenous infusion rate of the placebo are the same as the investigational medicinal product (IMP).

Continuous cardiac monitoring during the period of IMP/placebo infusion is required as systemic toxicity can provoke cardiac arrhythmias.

The planned duration of infusion will be determined pre-operatively by the participating unit’s normal postoperative availability of continuous cardiac monitoring. Units where normal postoperative disposal is to the standard inpatient ward, where facility for cardiac monitoring is not available, will aim to administer the infusion for a minimum of 6 h (operating time plus theatre recovery suite time). Before the patient is moved to the ward, the infusion will be stopped. This means that (i) if the operating time plus theatre recovery suite time is less than 6 h, the duration of the infusion will also be less than 6 h, and (ii) if the operating time plus theatre recovery time is 6 h or more, the duration of the infusion will be more than 6 h but will be stopped before 12 h.

Units where normal postoperative disposal is to HDU, or other clinical area where cardiac monitoring is available, will aim to administer the infusion for up to 12 h. If the patient is moved to a ward without cardiac monitoring facilities before the 12-h period has been completed, the infusion will be stopped.

#### Criteria for discontinuing or modifying allocated interventions {11b}

As noted above (in the “Intervention description {11a}” section), the infusion will run for a maximum of 12 h but will be stopped if continuous cardiac monitoring is stopped before the end of the planned duration. Infusion of lidocaine will be stopped immediately if the patient has symptoms of acute systemic toxicity. The treatment of systemic lidocaine toxicity is supportive treatment and lipid rescue.

#### Strategies to improve adherence to interventions {11c}

The IMP/placebo infusion will be monitored as a part of standard nursing care for patients. As the IMP/placebo is infused for a maximum of 12 h, all participants will be inpatients throughout the infusion. Infusion rate tables have been provided to local study teams to minimise user error in administrating the IMP to participants.

#### Relevant concomitant care permitted or prohibited during the trial {11d}

Concomitant continuous infusions of local anaesthetic agents are prohibited to prevent cumulative systemic toxicity; hence, planned epidurals or continuous infusion of local anaesthetic via wound catheters are both exclusion criteria.

#### Provisions for post-trial care {30}

This is a one-off infusion given to participants during surgery and post-operatively. Usual care for participants continues throughout the surgery and post-operative period, during their recovery and after discharge.

### Outcomes {12}

Return of GI function after surgery is awkward to define. A variety of endpoints are reported in studies (nausea scores, time to passage of flatus, time to passage of stool, time to normal oral intake, etc.). Previous studies of return of GI function after colorectal surgery described and validated composite clinical endpoints (GI-3 and GI-2) and were validated by the authors in a separate feasibility study prior to ALLEGRO [1, 2, 16].

#### Primary outcome

The primary outcome is achievement (yes/no) of GI-3 recovery (a composite endpoint defined as the achievement of both of the following two events: tolerating diet without significant nausea or vomiting for three consecutive meals; AND passage of flatus OR stool) at 72 h after the start of operation.

#### Secondary outcomes

Time to GI-3 recoveryTime to GI-2 recovery (a composite endpoint defined as time from surgery to the time to establish both of the following two events: tolerating diet without significant nausea or vomiting for three consecutive meals; AND first passage of stool).Rate of prolonged postoperative ileus (failure to establish GI-3 by 120 h after surgery)Nausea and vomiting scoreOverall Benefit of Analgesia (OBAS) scoreTotal postoperative opioid consumptionQuality of recovery (QoR-15 patient-reported outcome measurement (PROM))EQ-5D-5L quality of life assessmentEnhanced Recovery After Surgery (ERAS) protocol complianceAnalysis of cost of care derived from hospital records, recorded GP visits and participant reported data up to 90 daysCost per quality-adjusted life years (QALYs) as observed over the 90 day trial period, and as modelled over longer termTotal length of hospital stay (primary admission plus any readmission(s))Mortality at 30 and 90 daysMajor complicationsRecord linkage analysis of survival (cancer-specific outcome data in appropriate patients up to 10 years)

### Participant timeline {13}

### Sample size {14}

In a feasibility study in laparoscopic colectomy conducted under real-world NHS conditions with NHS patients typical of the recruitment cohort proposed in this application, 22 of a total of 50 patients (44%) failed to achieve return of GI function (GI-3 endpoint) by the third postoperative day [2]. Ten patients (20%) went on to develop prolonged postoperative ileus (PPOI). Interpretation of data from other healthcare systems is made complex by reporting of various univariate endpoints, but control arm data support this event rate. Effect size in published reports ranges from 15 to 40% relative reduction in GI dysfunction rate, again using a variety of univariate endpoints.

Therefore, with a sample size of 562 randomised 1:1 to IV lidocaine or placebo the study will have 90% power at a two-sided 5% level of significance to detect a relative reduction of 33% from 40 to 26.8% (absolute reduction of 13.2%) in non-return of gut function at 3 days post-operatively (or if the event rate is lower, the same power to detect a 40% relative reduction from 30% to 18% (a 12% absolute reduction)). Given the primary endpoint is measured in hospital, there should be no appreciable loss to follow-up (the perioperative death rate is ~ 1% for the whole duration of hospital stay and the very few discharged before 3 days can be assumed to have achieved return of GI function). This size of study would also give similar power to detect a difference of 10% (from 20% to 10%) in the important secondary outcome of PPOI.

### Recruitment {15}

Eligible individuals are identified by their usual clinical team from planned elective operating lists and given a patient information sheet. Eligibility is confirmed, consent received, baseline details collected, and randomisation performed pre-operatively, where possible, at routine hospital visits.

As noted above (in the “Who will take informed consent? {26a}” section) where a face-to-face visit is not possible to carry out the recruitment procedures, participants can complete the consent form at home and either post it back to the research team or bring it into hospital with them when they are admitted for surgery. In such cases, eligibility is confirmed, baseline details collected, and randomisation performed pre-operatively.

### Assignment of interventions: allocation

#### Sequence generation {16a}

Following consent, a minimisation algorithm is used to randomly allocate participants (on a 1:1 basis) to receive intravenous lidocaine or placebo. This is available using a web-based application (available 24 h a day). The minimisation criteria are age (< 50 years, 50–74 years, 75 years and older), gender and trial centre.

#### Concealment mechanism {16b}

The web-based randomisation system ensures allocation concealment.

#### Implementation {16c}

The allocation sequence generation is embedded in the trial web site. Research nurses based at sites enrol participants and randomise them using the web-based randomisation system.

### Assignment of interventions: blinding

#### Who will be blinded {17a}

Participants, medical staff, local pharmacy staff and study staff/outcome assessors are all blinded in this study. Both study drug and placebo are clear colourless liquids packaged in identical containers by the manufacturer. At randomisation, the participant will be allocated a unique participant study number and assigned a numbered participant study drug pack. Randomisation also triggers a notification email to the local clinical trials pharmacy to provide the numbered pack to the local study team on receipt of a signed clinical trials prescription.

#### Procedure for unblinding if needed {17b}

In the event of the characteristic symptoms of lidocaine toxicity in a trial patient, it is appropriate to stop the infusion and treat as per current Association of Anaesthetists of Great Britain and Ireland guidelines without having to wait for code breaks/permissions etc. If necessary, the investigator can unblind a participant’s treatment allocation via the trial database or telephone. All investigators receive training on this prior to the site opening to recruitment.

### Data collection and management

#### Plans for assessment and collection of outcomes {18a}

Data are collected at baseline and at 1, 2, 3, 4, 5, 6 and 7 days after surgery, at discharge from hospital and at 30 and 90 days after surgery. The schedule for data collection is summarised in Table 1.

**Table 1 Tab1:** Schedule for data collection

Assessment	Recruitment/baseline	POD 1	POD 2	POD 3	Daily from POD 4 until discharge	POD 7	Discharge	30 days	90 days
Assessment of eligibility criteria	✓								
Written informed consent	✓								
Pregnancy test (where applicable)									
Demographic data, contact details	✓								
Clinical history/past medical history	✓								
Drug history esp. laxatives	✓								
Height	✓								
Weight	✓	✓							
p-POSSUM	✓	✓ (part)						✓ (part)	
Operation type		✓							
Duration of operation		✓							
Blood loss (ml)^a^		✓							
OBAS score	✓	✓	✓	✓	✓	✓			
QoR score	✓	✓	✓	✓	✓	✓		✓	
PONV score		✓	✓	✓	✓				
EQ-5D-5L	✓	✓	✓	✓	✓	✓		✓	✓
CRP^b^	✓		✓	✓					
Time to first flatus			✓	✓	✓				
Time to first bowel movement			✓	✓	✓				
Time to tolerating solid food			✓	✓	✓				
antiemetic dose total up to 72 h							✓		
Total number of episodes vomiting		✓	✓	✓					
Total opioid consumption in-hospital up to 72 h							✓		
ERAS protocol compliance		✓	✓	✓					
Achievement of medical criteria for discharge Y/N				✓	✓				
Patient-reported readiness for discharge				✓	✓				
Length of stay (days)							✓		
Complications							✓	✓	
Unplanned readmissions								✓	
Mortality							✓	✓	✓
Adverse events		✓	✓	✓	✓	✓		✓	
Concomitant medications	✓	✓	✓	✓	✓	✓		✓	

^a^Millilitres

^b^C-reactive protein

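### Three secondary outcomes (time to GI-2, total opioid use, and readmission with total stay) reach beyond the data that Table 1 schedules

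*Protocol article*

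**What the plan says.** **GI-2.** Under Secondary outcomes, time to GI-2 needs the diet criterion and a first stool, with no end of follow-up given. Under Primary outcome, GI-3 uses the same diet criterion but accepts flatus or stool. In Table 1 the row "Time to first bowel movement" is ticked at POD 2, at POD 3 and in the column "Daily from POD 4 until discharge". It is not ticked at POD 7, 30 days or 90 days. Section {18b} provides a telephone call at 7 days for anyone discharged before reaching the primary endpoint. Section {20a} assigns Cox regression to time-to-event outcomes.

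**Opioids.** The Secondary outcomes list names total opioid use after surgery, without a limit. The Table 1 row is "Total opioid consumption in-hospital up to 72 h", ticked in the Discharge column.

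**Readmission and stay.** The objectives in section {7} count unplanned readmissions within 30 days of leaving hospital. The Secondary outcomes list defines total stay as the primary admission plus any readmission. In Table 1, "Unplanned readmissions" has a single tick at 30 days, and section {18a} counts its 30- and 90-day contacts from surgery. Length of stay is ticked only at discharge. At 90 days only EQ-5D-5L and mortality are ticked. Section {20a} refers to Table 1 for the health care resource use that feeds the cost analysis.

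**The concern.** An analysis plan can choose a model or a censoring rule, but it cannot recover times or amounts that were never collected.

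For GI-2 the issue is bias. The Background says that discharge follows recovery of gut function. Leaving hospital is therefore not an independent censoring event, and the Cox model assumes that it is.

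For opioids the outcome's name promises more than the row delivers. The window also closes earlier for anyone who goes home before 72 h, and the trial hopes that lidocaine will make earlier discharge more common.

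For readmissions the single scheduled contact comes before the objective's own window has closed, and no later item is scheduled to complete total stay.

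**Working it through.** **1. The plan's own figure.** The sample size section states "with a sample size of 562 randomised 1:1 to IV lidocaine or placebo the study will have 90% power at a two-sided 5% level". With pooled variance, the size per arm is

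n = [1.96·√(2p̄(1−p̄)) + 1.2816·√(p₁(1−p₁) + p₂(1−p₂))]² / (p₁−p₂)²,

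and the continuity-corrected size per arm is (n/4)·[1 + √(1 + 4/(n·|p₁−p₂|))]².

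| Contrast | Total N, uncorrected | Total N, corrected | Power at 281 per arm, uncorrected |
|---|---|---|---|
| 40% v 26.8% | 534 | 564 | 91.5% |
| 30% v 18% | 530 | 562 | 91.7% |
| 20% v 10% (prolonged ileus) | 532 | 572 | 91.5% |

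The stated 562 reproduces with the continuity correction, to within rounding or about 2%. Nothing below changes it.

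**2. GI-2.** Let D be the time of discharge and S the time of first stool.
- A patient who meets the diet criterion and passes flatus has reached GI-3 and can go home. If S > D, GI-2 is still open.
- The stool row has stopped by then. The 7-day call is not described as covering this patient, who has already met the primary endpoint. The GI-2 time is censored at D.
- At D this patient lacks only stool, whereas some of those still in hospital have not yet tolerated food. The discharged patient is closer to GI-2 than those left in the risk set, so the censoring is likely to be informative.
- A hazard ratio above 1 favours lidocaine here, because the event is recovery. If lidocaine shortens the interval from GI-3 to discharge, more near-events are removed from that arm and the ratio falls.

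The direction can be illustrated by simulation. Every input is an assumption and none comes from the protocol: half of patients pass stool after GI-3, with a mean gap of 24 h, and the mean time from GI-3 to discharge is 24 h on placebo.

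| True effect on GI-3 | Mean GI-3 to discharge, lidocaine | GI-2 hazard ratio, censored at discharge | With full follow-up |
|---|---|---|---|
| None | 24 h | about 1.00 | 1.00 |
| None | 12 h | about 0.93 | 1.00 |
| Times 20% shorter (median 66 h, log-SD 0.6) | 24 h | about 1.37 | about 1.35 |
| Times 20% shorter | 12 h | about 1.28 | about 1.35 |

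The bias is negligible when the interval is the same in both arms and runs against lidocaine when the interval is halved. The protocol gives neither the share discharged after flatus and before stool nor the interval by arm, so the actual size cannot be computed.

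**3. Opioids.** The recorded quantity is use from surgery to min(72 h, D). Someone leaving at 48 h contributes 48 h, which is 72 − 48 = 24 h less than someone still in hospital at 72 h. Use after 72 h enters no total. Concomitant medications are ticked to 30 days, but no opioid total is scheduled from that row.

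**4. Readmission.** For a stay of d days, the objective's window closes on day d + 30 after surgery. With the 4 to 6 day stay in the Background, that is 4 + 30 = 34 to 6 + 30 = 36. The only tick is at day 30, which is 4 to 6 days short. Total stay has no stated limit on readmissions, and no row covers them after that tick.

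**5. What is not touched.** Prolonged ileus is judged at 120 h (day 5), before the 7-day call at 7 × 24 = 168 h. GI-3 at 72 h is covered in hospital or by that call.

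**The case against.** The strongest reply is that Table 1 is a summary within an article that condenses a fuller protocol, so an empty cell does not prove that nothing is collected. The 7-day collection of the primary endpoint itself has no tick in the GI rows. This has force for details of cost data, but less for GI-2, where the text says what the 7-day call is for and first stool is not included.

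Four stronger readings are tempting, and the document does not support them.

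- **The 90-day cost analysis is truncated.** A reader might infer this from the lack of readmission, GP or nurse items after day 30. However, the Secondary outcomes list names hospital records, GP visits and participant reports to 90 days as sources, and section {20a} leaves detail to a health economic analysis plan. Records can be extracted without a visit tick. What remains is that section {20a} cites Table 1 for resource use and Table 1 has no such item at 90 days.
- **The opioid comparison is materially tilted towards lidocaine.** The sample size section expects very few discharges before 3 days, and the Background says most patients need little or no analgesia by 48 to 72 h. Any shift is probably small.
- **A definite share of GI-2 times is lost, or GI-2 is biased in lidocaine's favour.** No share can be derived, and the plausible direction is the opposite.
- **All GI outcomes are exposed.** Only the stool component of GI-2 is.

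It is also fair to note that section {18b} allows visit windows around the calls. A late 30-day call might reach some of the missing readmission days, but the widths are not given.

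**Conclusion.** The point holds for three secondary outcomes.

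1. No stated collection covers first stool after discharge once GI-3 has been met, so time to GI-2 would be censored at a time that depends on gut recovery. A bias against lidocaine follows if lidocaine also shortens the time from GI-3 to discharge. That is an assumption, and the size is unknown.
2. The opioid outcome is named as a total, but the data are in-hospital use to the earlier of 72 h and discharge. The mismatch in definition is certain; its numerical effect is probably small.
3. The single readmission tick falls about 4 to 6 days short of the objective's window and does not support a total stay that counts every readmission. The reference to Table 1 for resource use leads to no 90-day item.

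The primary outcome, prolonged ileus and the sample size stand. Loss of 90-day cost data is not shown.

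**What to change.** - **GI-2:** at the existing POD 7 call, record the date and time of first stool for every participant discharged without it.
- **Opioids:** restate the outcome as in-hospital use to 72 h and make the window equal for all, either by asking at POD 7 about opioids taken between discharge and 72 h or by analysing a fixed earlier window.
- **Readmission, stay and resource use:** add readmissions and inpatient days to the existing 90-day call, or state the hospital-records extraction that supplies them. Reconcile the two origins of the 30-day window (surgery in section {18a}, discharge in section {7}), and correct the reference in section {20a} so that it points to where 90-day resource use is scheduled.

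The cost is a few questions in calls already planned and one amendment to the schedule. Answers about stool and opioids will carry some recall error. Recruitment opened in August 2018 and was due to close in December 2022, so participants already past these contacts cannot be asked and coverage would be partial. Restating the opioid outcome and naming a records extraction do not depend on new contacts.

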#### Plans to promote participant retention and complete follow-up {18b}

Data are collected at routine clinic/hospital appointments and in hospital during postoperative recovery. It is highly unlikely that any patient will be discharged from hospital prior to achieving the primary endpoint; in such cases, this will be collected by phone at 7 days. For the participant reported outcomes collected (by telephone) at 7, 30 and 90 days after surgery, there is an acceptable visit window within which this data can be collected. We will aim to collect outcome data on all participants randomised, regardless of whether or not they received the intravenous lidocaine/placebo. There are no additional plans to enhance retention in ALLEGRO.

#### Data management {19}

All data are captured onto a paper-based case report form and entered by site staff onto a web-based case report form. All data are held securely on a server at the University of Aberdeen. The central trials team monitor data entry and ensure that missing or erroneous data are addressed as soon as possible after detection.

#### Confidentiality {27}

Data are stored in accordance with GCP and with the UK Data Protection Acts 1998 and 2018.

Unique participant identifiers (study number) are used to identify completed case-report forms and questionnaires. Records are kept in a secure storage area with limited access.

The Trial Website is secure sockets layer (SSL) secured, ensuring links between server and browser client are always encrypted. Access to patient identifiable information is limited to key personnel only and has appropriate user level access across a secure network, personal identifiable data held in the database will be encrypted to advanced encryption standard AES_256.

#### Plans for collection, laboratory evaluation and storage of biological specimens for genetic or molecular analysis in this trial/future use {33}

Not applicable—there are no biological specimens within this study.

### Statistical methods

#### Statistical methods for primary and secondary outcomes {20a}

Analysis will be by intention to treat. All baseline and outcome data will be described using appropriate summary statistics, e.g. frequency and proportions for dichotomous data, mean and standard deviation for continuous data (or median and interquartile range if more appropriate), and graphical methods. The primary outcome will be analysed using a generalised linear model with a logit link function and including minimisation covariates. Secondary outcomes will be analysed in a similar manner using a statistical model appropriate for the outcome (Cox regression for time-to-event outcomes, linear regression for continuous outcomes). All treatment effects will be presented with 95% confidence intervals. The planned analysis will be documented in the statistical analysis plan prior to analysis starting.

Full details of the Health Economic analysis will be specified in a Health Economic Analysis Plan prior to analysis [17]. Two complimentary forms of analysis will be undertaken: (1) a within trial analysis utilising self-reported EQ-5D-5L data, and health care resource utilisation (HCRU) extracted from hospital records detailed in Table 1 [schedule for data collection in the “Plans for assessment and collection of outcomes {18a}” section], undertaken via generalised linear modelling and a recycled predictions approach [18] to account for skew, and (2) simplified decision analytic modelling [19] incorporating any available wider literature [6] for longer term outcomes and low frequency high severity events.

To maximise UK policy relevance, both health economic analysis will follow National Institute for Health and Care Excellence (NICE) reference case recommendations [20] including adoption of an NHS and personal social service (PSS) costing perspective for primary analyses; application of standard UK price weights to HCRU to estimate cost [21, 22]; a cost-utility approach (results presented in terms of incremental cost per quality-adjusted life year (QALY), with QALYs derived from EQ-5D-5L); discount rate of 3.5% for both costs and QALYs (if applicable); use of probabilistic sensitivity analysis (PSA) to generate cost-effectiveness acceptability curves [18, 19] and deterministic sensitivity analysis on key assumptions where PSA is inappropriate.

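### The models described for OBAS, QoR-15 and EQ-5D-5L name only the minimisation factors as covariates, although each instrument is scored at baseline; adding that score would gain precision at no cost

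*Protocol article*

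**What the plan says.** In the protocol article, Statistical methods for primary and secondary outcomes {20a}, the primary outcome is modelled by a generalised linear model with logit link that contains the minimisation covariates. Sequence generation {16a} lists these as age in three bands, gender and trial centre. The same statistical section continues: "Secondary outcomes will be analysed in a similar manner using a statistical model appropriate for the outcome". Linear regression is named for continuous outcomes and Cox regression for times to event. No further covariate is mentioned. The paragraph ends by leaving documentation of the planned analysis to the statistical analysis plan.

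Outcomes {12} lists OBAS, QoR-15 and EQ-5D-5L as secondary outcomes. Table 1 ticks all three in the recruitment/baseline column and again after surgery: OBAS to day 7, QoR to 30 days and EQ-5D-5L to 90 days.

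The economic evaluation has its own paragraph. It describes "a within trial analysis utilising self-reported EQ-5D-5L data" together with resource-use data, fitted by generalised linear modelling with recycled predictions. It lists no covariates and leaves full details to a Health Economic Analysis Plan.

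**The concern.** A protocol may leave covariates to the analysis plan. This one goes further: it names a set for the primary outcome and carries it to the secondary outcomes by reference. The primary endpoint has no baseline value, so its covariate set contains no baseline score. An analyst who takes the same set into the linear regressions would leave out what may be the most useful predictor of each patient-reported score, namely the patient's own earlier score on the same instrument. The only use the article describes for the baseline data is descriptive summary.

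What is at stake is precision. Confidence intervals for these outcomes would be wider than they need to be, and a modest real difference would be easier to miss.

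**Working it through.** **Inputs from the protocol article.** Sample size {14} plans "with a sample size of 562 randomised 1:1 to IV lidocaine or placebo", which is 281 per arm, and says that "the study will have 90% power at a two-sided 5% level of significance".

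**The plan's own figure.** For 40% versus 26.8%, the pooled-variance formula for two proportions is n = [1.960·√(2p̄(1−p̄)) + 1.282·√(p₁(1−p₁)+p₂(1−p₂))]² / (p₁−p₂)², with p̄ = 0.334. This gives 267 per arm, 534 in total. With the continuity correction it gives 564. For 30% versus 18% the totals are 530 without the correction and exactly 562 with it. The stated size is therefore reproduced. It rests on the binary primary endpoint and does not depend on how the secondary models are adjusted.

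**Inputs not in the article.** The correlation r between baseline and follow-up score is not given. It is taken here as the correlation that remains after treatment and the minimisation factors are in the model, and is varied from 0.1 to 0.7. The article expects for the primary endpoint that "there should be no appreciable loss to follow-up", but gives no completeness figure for the patient-reported scores. So 281 per arm is an upper limit for them; the ratios below do not depend on it.

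**Formulae, in units of the outcome SD.**
- Standard error without the baseline score: √(2/281) = 0.0844; 95% half-width 1.96 × 0.0844 = 0.1654.
- Standard error with the baseline score: 0.0844 × √(1 − r²).
- Variance inflation from leaving it out: 1/(1 − r²).
- Equivalent total size: 562/(1 − r²).
- Power with the baseline score, for an effect that has 80% power without it: Φ[(1.960 + 0.842)/√(1 − r²) − 1.960].

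| r (assumed) | Variance inflation if omitted | SE ratio, with/without | 95% half-width with baseline (SD) | Equivalent N | Power, from 80% |
|---|---|---|---|---|---|
| 0.1 | 1.010 | 0.995 | 0.1645 | 568 | 80.4% |
| 0.3 | 1.099 | 0.954 | 0.1577 | 618 | 83.6% |
| 0.5 | 1.333 | 0.866 | 0.1432 | 749 | 89.9% |
| 0.7 | 1.961 | 0.714 | 0.1181 | 1102 | 97.5% |

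For example, at r = 0.5, 562/0.75 = 749, and Φ(2.802/0.866 − 1.960) = Φ(1.275) = 0.899.

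**Reading the table.** The gain is negligible at r = 0.1 and material from about r = 0.5. OBAS rates the benefit of analgesia, and its baseline is taken before the operation, so its correlation with postoperative scores is probably at the low end. One extra covariate with 281 per arm costs essentially nothing even then.

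**The case against.** The strongest reply is that the article does not fix the covariates for these outcomes. It says that the minimisation factors are included, not that they are the only terms. Similar does not mean identical, and a model suited to the outcome may well contain a baseline term where one exists. The list of covariates for each secondary outcome is ordinary analysis-plan content, the article defers to that plan, and neither it nor the full protocol was available here. Much of this stands: a reader might infer that baseline scores are excluded, and the text does not say so. What remains is that the only covariates named are carried over by reference from an endpoint without a baseline, so the wording steers towards the less precise model.

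Two stronger readings are tempting and are not supported.

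- *The QALY analysis ignores baseline utility.* The sentence on secondary outcomes does not govern the economic models. Those are described separately, with no covariates listed, and regression with recycled predictions can accommodate baseline utility. The amount involved would be 0.2 × √(2/281) = 0.017 in utility for one standard error of chance imbalance, if the baseline SD were 0.2 (assumed). Over 90 days that is 0.017 × 90/365 ≈ 0.004 QALY if carried over in full, or about 0.002 at a slope of 0.5. The article gives no expected QALY gain to set beside this, and no omission is shown.
- *Chance baseline imbalance biases the comparison.* Under randomisation it does not do so on average. It adds random error that the unadjusted interval already reflects. Adjustment removes the shift in the realised trial and narrows the interval.

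**Conclusion.** The point holds as a low-severity recommendation on precision for three patient-reported secondary outcomes. If the models are fitted with the named covariates alone, the variance of the treatment difference is larger by about 1%, 10% or 33% at r = 0.1, 0.3 or 0.5. These correlations are assumptions, so the loss for each instrument cannot be read from the article. The estimates remain valid. The primary outcome and the sample size are unaffected. The article does not establish that baseline scores will be left out, only that it names no place for them in the models; the analysis plan may already settle this.

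**What to change.** State, in the analysis plan or by a one-line clarification, that the linear models for OBAS, QoR-15 and EQ-5D-5L each include the baseline score of the same instrument beside age band, gender and centre. Add a simple rule for missing baselines, either mean imputation or a missing-value indicator, so that no randomised participant is dropped for lack of one. Record this before the analysis starts, so that the adjustment is prespecified. The cost is one sentence and one covariate per model; Table 1 already schedules the data, and no change to sample size or visits is needed.
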